# Objectives and Research Aims

Given the importance of health financing for access to and appropriate utilization of care, especially for chronic conditions, we are submitting a sub-study of the previously accepted protocol, “Health systems governance for an inclusive and sustainable social health protection in Tanzania.” The overall aim of our study is to explore the implementation process of health financing policy and social health protection schemes in Tanzania. In doing so, this study seeks to improve the equity of access to chronic care and inform the improvement of health financing policy so that Tanzania may work towards achieving more equitable financing schemes inclusive of vulnerable and marginalized population groups. In this phase of the study, we will expand upon the specific study objective *to identify challenges hindering the existing social health protection schemes from enabling poor and vulnerable groups accessing quality health care* with four specific objectives:

1. to quantify the direct and indirect cost associated with accessing NCD care services, and describe strategies for coping with the cost burden
2. to understand the differences between people with NCDs who are engaged in care and those that are not

To address these aims we will investigate the following research questions.

### Research Question 1

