#### *Exit survey*

The patient health facility exit survey will be administered to patients at all tertiary and secondary health facilities, and a corresponding sample of 8 dispensaries in both the Kilombero district and Same district. As each of these districts has 8 health centres, dispensary sampling will be matched by randomly selecting 1 dispensary from each ward containing a health centre.

The patient exit survey will be delivered at health facilities to adult patients seeking outpatient care. Target sample size was designed to be representative of patents visiting the health facilities for outpatient care for all conditions included NCDs. Hospital and health centre outpatient clinics typically designate one day per week as an ‘NCD day’, when a medical officer is assigned to be available to provide outpatient NCD care. As such, for each sampled hospital and health centre, the exit surveys will be delivered on one health facility NCD day to ensure that sufficient numbers of patients with NCDs can receive the questionnaire, and on one clinic day not designated for NCD care so as to also collect a more typical sample of people seeking outpatient care. Some rural health facilities, especially dispensaries which might not offer an NCD clinic day, might have low numbers of patients specifically visiting for chronic disease care, but this is representative of the typical clinical makeup and should be measured.

Rather than random or systematic random sampling, this study will use the more operationally efficient method of selecting and recruiting patients based on the order in which they enter the consultation room. As demonstrated by Geldseltzer et al. (2016), sampling patients as they enter the consultation room is advantageous as it is more efficient and simple to implement than random sampling approaches, and it minimises the bias of consultation length that is associated with sampling patients as the exit the consultation room [10].

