It is expected that with 2 field workers per health facility, 36 patients can be interviewed per day at hospitals and health centres, while 1 one field worker is expected to be able to interview 12 patients per day at each sampled dispensary. If patient volume is too low to meet this daily requirement, field workers will return later to the same facility to ensure the sample size is reached. As such, across both districts, we are anticipating a total sample size of 1,632 for the exit survey (Table 1), generously exceeding the minimum sample size that was previously indicated. Participants will be recruited while waiting to enter the consultation room, and the research assistant will administer the questionnaire after the participants has seen the clinician so as to avoid disrupting the work flow at the clinic.

The questions asked in the exit survey will mostly be the same as those asked in the household survey, so that household survey respondents will serve as the general population with which people accessing NCD care can be compared. However, in the exit surveys, additional questionnaire items will be included relating to the specific services being utilised on the day of the health facility visit. The questionnaire will take on average 20 minutes to complete. If during the piloting phase the questionnaire takes too long to complete, we will reduce the number of questions asked from the accepted survey, prioritizing questions that best reflect the explicit research questions.

**Table 1: Sample size and sampling strata.** Sample size calculated based on a hypertension prevalence of 19.9% (95% CI: 17.1-22.9) for rural Tanzania [11], population estimates from the Tanzania 2012 census, and a benchmark mean annual household health expenditure of 30,000 Tanzanian shillings by using a modified Cochran sample size calculation.

| **Study Type** | **Sample Size** | **Strata** |
| --- | --- | --- |
| Exit Interviews |  | Kilombero District:   - 18 health facilities |
|  | 72 per hospital | - 2 hospitals |
|  | 72 per health centre | - 8 health centres |
|  | 12 per dispensary | - 8 dispensaries |
|  |  | Same District:   - 18 health facilities |
|  | 72 per hospital | - 2 hospitals |
|  | 72 per health centre | - 8 health centres |
|  | 12 per dispensary | - 8 dispensaries |
|  | **Total: 1,632** | **Total: 36 health facilities** |
| Household Survey |  | Kilombero District: |
|  | 15 households | Ifakara town |

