### Analytical Methods

By delivering a household survey to the general populations of Kilombero and Same, and an exit survey to people accessing NCD services, we will be able to comparatively analyse the specific challenges and coping mechanisms that people living with NCDs face in accessing services, in relation to the general population.

The data collected from the household survey and exit survey will first be analysed using descriptive statistics to investigate the burden of OOPs and economic losses associated with living with hypertension and/or diabetes, and to determine how much households spend upon the direct and indirect costs of accessing NCD care. General hypotheses related to the geographic and economic accessibility of health care, such as whether distance from a health facility is associated with direct and indirect healthcare costs, and whether distance from a health facility moderates the association between social health protection and household health expenditure, will be explored using linear mixed models and analyses of variance.

We will quantify the proportion of the household survey respondents who were hypertensive or diabetic, and not aware of their condition or not enrolled in care. We will then use univariate and multivariate logistic regression analyses to identify differences between the household respondents with an NCD who are not enrolled in care and NCD patients from the exit interviews who are enrolled in care. We will quantify systematic and individual characteristic predictors of willingness-to-pay for NCD care and social health protection schemes for people in care for non-NCD reasons, for NCD reasons, and household respondents.

A regression model will then be used to assess whether living with hypertension and/or diabetes is associated with financial hardship, and/or illness-related economic and productivity losses, using the indicators catastrophic health expenditure and impoverishment. An analysis of variance (ANOVA) of mean spending by revenue source will then be used to determine the relative importance of financial contributions from various household revenue streams to covering the costs of NCD care, such as:

- Earnings from work (informal or formal)

- Selling personal property (clothing, bicycle, furniture, etc.)

- Financial contributions from the social network (friends, family, neighbours, etc.)

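### The in-care versus not-in-care regression draws each group from a different survey, so its odds ratios for distance, cost and utilisation are open to a selection bias the plan has no means of detecting

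*Protocol*

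**What the plan says.** Objective 2 is "to understand the differences between people with NCDs who are engaged in care and those that are not" (Protocol, Objectives and Research Aims). The Analytical Methods section fixes the model, a logistic regression fitted first with single predictors and then with several. It also fixes the two groups to be compared: "household respondents with an NCD who are not enrolled in care and NCD patients from the exit interviews who are enrolled in care". It names no weights, no check on survey source and no comparison within one survey.

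The two surveys are sampled differently.

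- **Households** (Household survey; Study Design). In each district, 15 households come from the town and 15 from each of 25 randomly selected villages. Blood pressure and random blood sugar are measured in respondents who accept.
- **Exit patients** (Exit survey; Table 1). Patients are taken in order of entry to the consultation. Every hospital and health centre has the same quota: "36 patients can be interviewed per day at hospitals and health centres", on one NCD day and one other day. One dispensary is drawn from each ward that has a health centre. The survey is described only as a questionnaire, mostly shared with the household survey, and "household survey respondents will serve as the general population with which people accessing NCD care can be compared".

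The protocol describes the exit sample in two ways. Analytical Methods speaks of "an exit survey to people accessing NCD services", while the Exit survey section says "The patient exit survey will be delivered at health facilities to adult patients seeking outpatient care", for all conditions.

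**The concern.** Every person not in care is a household respondent and every person in care is an exit patient. A term for survey source cannot be fitted, because it equals the outcome. Anything that makes a person in care more or less likely to be met at a clinic exit therefore enters the coefficients and cannot be seen from within the model.

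This matters most for predictors that describe access. Distance, cost and utilisation may affect whether someone is in care, and they may also affect how often and where an in-care person attends. The way an NCD is identified differs too: households can contribute people found by measurement, while exit patients are people attending a clinic.

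This regression is the only stated direct comparison of engaged with non-engaged people. Findings on barriers to care would be read from it.

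**Working it through.** **1. The exit sample.** Per district (Table 1): 2 × 72 + 8 × 72 + 8 × 12 = 816. Two districts: 2 × 816 = 1,632, which reproduces the protocol's figure ("we are anticipating a total sample size of 1,632 for the exit survey"). Of these, 2 × 10 × 72 = 1,440 (88%) are fixed quotas at hospitals and health centres, whatever the facility's volume. By plan, 2 × 10 × 36 = 720 (44%) fall on NCD days.

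**2. When the design biases an odds ratio.** Take a binary predictor, and let r be the probability of exit sampling for exposed in-care people divided by that for unexposed in-care people. Exit sampling multiplies the exposure odds in the in-care group by r and leaves the not-in-care group unchanged, so

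observed OR = true OR × r.

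| True OR | r = 1 | r = 1.5 | r = 2 | r = 3 |
|---|---|---|---|---|
| 1.0 | 1.0 | 1.5 | 2.0 | 3.0 |
| 1.5 | 1.5 | 2.25 | 3.0 | 4.5 |
| 2.0 | 2.0 | 3.0 | 4.0 | 6.0 |

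A simulated logistic regression adjusting for one other covariate agreed. With r = 1 it gave 0.98, 1.46 and 2.01 for true values of 1.0, 1.5 and 2.0. With a true OR of 1.0 and r = 1.5, 2 and 3 it gave 1.50, 2.00 and 3.00, so the adjustment did not remove the bias.

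**3. What the documents say about r.** They give no value, so the values above are assumptions. A value below 1 would bias the other way. Four design features make r = 1 doubtful for access-related predictors:

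- Sampling is per visit. If inclusion is proportional to visits, a monthly attender is 12/4 = 3 times as likely to be met as a quarterly one. Were 30% of in-care patients monthly attenders and 70% quarterly (assumed), monthly attenders would form 0.3 × 12 / (0.3 × 12 + 0.7 × 4) = 56% of the exit sample. This shifts an odds ratio only as far as visit frequency is related to the predictor.
- Quotas are equal across hospitals and health centres, so patients of low-volume sites are over-represented.
- One of the two planned days at each of these sites is an NCD day.
- Dispensaries come only from wards with a health centre, whereas the villages are randomly selected. This bears directly on distance.

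The protocol's reason for sampling at entry concerns consultation length. It does not address visit frequency.

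**4. What a within-household contrast could offer.** The text gives 390 households per district, so 780 in all (2 × 26 × 15 = 780; Table 1 prints 790). Assume one tested respondent per household. At the protocol's hypertension prevalence of 19.9% this gives 780 × 0.199 = 155, or 133 to 179 over its interval of 17.1–22.9%. The share in care is not given:

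| Assumed share in care | In care | Not in care |
|---|---|---|
| 20% | 31 | 124 |
| 30% | 47 | 108 |
| 40% | 62 | 93 |

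For an odds ratio of 2 with 40% exposure among those not in care (both assumed), a simple two-proportion calculation gives about 41% power at 20% in care and 51% at 30%. It ignores clustering by village.

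**The case against.** Drawing each outcome group from its own source is case-control sampling. A reader might infer that the odds ratios are biased simply because care status equals survey source. That does not follow: with r = 1 the true values are recovered. This part of the objection stands, and it confines the concern to predictors linked to exit sampling. The shared questionnaire also weakens any argument from differing instruments, and the number of blood pressure readings in the household is not stated.

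A reader might also infer that objective 2 has no other analysis. It has: Analytical Methods also plans the proportion of household respondents unaware or not in care, and predictors of willingness to pay. Neither needs this contrast. Nor are household in-care respondents lost to the study, since they remain available to the cost, willingness-to-pay and hardship analyses.

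Of the 1,632 exit interviews, 720 + 192 = 912 (56%) are planned for non-NCD days or dispensaries. It is tempting to read this as contamination of the regression. It is not, because the regression is restricted to NCD patients. The figure shows only that the description of the exit sample is loose, and the same section later separates patients attending for NCD and for other reasons.

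Finally, oversampling NCD days is a reasonable answer to scarce in-care cases, and weights are commonly left to a statistical analysis plan. Both points are fair. The contrast itself, however, is fixed in the protocol, and it leaves out the in-care respondents who share a sampling frame with those not in care.

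**Conclusion.** The concern holds in a limited form. Care status and survey source coincide, no source term can be fitted, and the exit design gives reason to expect that inclusion depends on access. Odds ratios for distance, cost and utilisation are therefore open to selection bias. The documents do not support a claim about its size or direction: the range of 1.5 to 3.0 for a true odds ratio of 1.0 rests wholly on assumed values of r. They also do not show that predictors unrelated to exit sampling are affected.

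A reader might conclude that the within-household contrast should become the primary analysis of this question. The figures do not compel that. With some 31 to 62 people in care, it exchanges bias for imprecision. The regression does not touch the sample-size outcome, household health expenditure. The changes rely mainly on data already planned, so they are worth making.

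**What to change.** In Analytical Methods:

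1. Add a logistic regression within the household survey of respondents with an NCD in care versus not in care. Show those aware but not in care separately from those unaware and screen-positive. Place it beside the exit-based contrast.
2. Include household in-care respondents in the in-care group of the existing model. This dilutes the selection but does not remove it. Every exit patient would still be in care, so a source term would remain inestimable in that model.
3. For that reason, compare household in-care with exit in-care patients separately, as a check on source effect.
4. Report distance, cost and utilisation coefficients from the exit-based model as subject to selection. Weight exit patients by inverse visit frequency if the exit questionnaire records it. The questionnaire is not shown, and the protocol allows items to be cut after piloting, so this must be confirmed.
5. Correct the description of the exit sample to adult outpatients for all conditions, with NCD patients as a subgroup.

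Items 1 to 3 and 5 need only analysis wording. The cost is wide confidence intervals for items 1 and 3, which should be stated in advance so that a null result there is not read as evidence of no difference.

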The second research question will aim to quantify the direct and indirect cost associated with accessing NCD care services, and describe strategies for coping with the cost burden. This includes determining which support systems people living with NCDs utilise, including their social networks, to cope with these costs. It will also seek to determine the cost of not having social health protection by comparing the total costs incurred between NHIF beneficiaries, iCHF beneficiaries, and those who are not part of a social health protection scheme. The role of patient social networks will be especially important to investigate, as it has been reported that people often attempt to capitalise on their social networks to avoid out-of-pocket expenditure (OOPs) by being added to another household’s iCHF membership, or by borrowing money from their social network [8]. Furthermore, this objective will take into account that although beneficiaries of social health protection may be less likely to experience financial hardship due to the direct cost of their illness, their illness may still impose a social and economic burden in the form of missed work days and lost income for either the individual living with the NCD, or their caregiver at times when one’s illness prevents them from working [9].

### Research Question 2

The third research question aims to understand the differences between people with NCDs who are engaged in care and those that are not. We aim to identify the proportion of the population that remains undiagnosed, and undertreated for hypertension and diabetes, and the barriers or perceived barriers to appropriately utilising NCD treatment compared with the patients who are accessing NCD care. In addition to socio-demographic and geographic mediators of care utilisation, we will quantify the willingness-to-pay for chronic disease care under different payment options, specifically out-of-pocket payments versus the payment of health insurance premiums, for both patients and individuals in the community.

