### Sampling Strategy and Sample Size

#### *Household survey*

We will conduct a household survey to collect information on household demographic and economic characteristics, health insurance and social protection, chronic illness, healthcare access and utilisation, household health expenditure, out of pocket payments for health care, and coping strategies to deal with diseases. In order to answer the key research question, information will be collected regarding direct and indirect household out-of-pocket expenditure (OOPs) on healthcare, how the household pays for their OOPs or social health protection premiums, economic productivity loss due to illness, recent healthcare utilisation, and the role of one’s social network in coping with illness. For respondents that accept, we will also measure blood pressure and random blood sugar to quantify undiagnosed and untreated hypertension and possible diabetes in the population. We will counsel patients with results outside of the normal range of the importance of following up with a healthcare provider to formally diagnose and initiate treatment if needed.

Using a stratified sampling approach, a household survey will be delivered throughout Kilombero and Same districts. In order to detect associations with the primary outcome of household health expenditure (power of 0.80, significance level of 0.05), a minimum sample size of 202 households per district is required. To calculate the minimum sample size, a household health expenditure of 30,000 Tanzanian shillings was used as a benchmark; corresponding to the cost of enrolling a household in the iCHF. However, in order to also answer research questions associated with our secondary objectives, we will seek a total sample size of 390 households per district.

As such, in each of Kilombero and Same district, 15 households from each district’s only town (Ifakara and Same, respectively), and 15 households from a random selection of 25 other villages will be sampled (Table 1).

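### The regression said to assess productivity losses names only catastrophic health expenditure and impoverishment as indicators, so it cannot properly test whether NCD status is associated with lost work and income

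*Protocol*

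**What the plan says.** The first specific objective is "to quantify the direct and indirect cost associated with accessing NCD care services". Under Research Question 1 the protocol explains what it means by the indirect part. It grants that "beneficiaries of social health protection may be less likely to experience financial hardship due to the direct cost of their illness", and then adds that "their illness may still impose a social and economic burden in the form of missed work days and lost income", whether for the patient or for a caregiver.

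The Household survey section lists "economic productivity loss due to illness" among the information to be collected. The Exit survey section says its questions will largely match those of the household survey.

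Three parts of Analytical Methods bear on this:

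- Descriptive statistics will cover out-of-pocket payments and economic losses in people with hypertension and/or diabetes, and are also meant "to determine how much households spend upon the direct and indirect costs of accessing NCD care".
- Linear mixed models and analyses of variance will explore, among other things, "whether distance from a health facility is associated with direct and indirect healthcare costs".
- "A regression model will then be used to assess whether living with hypertension and/or diabetes is associated with financial hardship", and/or with "illness-related economic and productivity losses, using the indicators catastrophic health expenditure and impoverishment".

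**The concern.** The third of these analyses is the only one that tests NCD status against productivity loss, and the indicators it names do not match that outcome. Catastrophic health expenditure is, by its name, a measure of spending. A person who pays little or nothing but stops working for a time can have a real productivity loss and no catastrophic expenditure.

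The study has a specific interest in that person. Research Question 1 singles out people with social health protection as likely to be spared direct cost while still losing work and income. If the sentence is followed as written, a weak or null association with the two indicators could be reported as a finding about productivity loss, although neither indicator measures it directly.

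**Working it through.** No sample size, power or significance level enters this point, and the plan gives no figure to reproduce. The check compares what the regression is said to assess with what its indicators can register.

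**Step 1: the constructs.** Research Question 1 treats hardship from direct cost and the burden of missed work and lost income as two things, and says the second can occur without the first. Analytical Methods puts both into one regression and names one pair of indicators.

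**Step 2: what the indicators register.** The protocol defines neither. Assume that catastrophic expenditure means health spending S relative to household resources R, compared with some threshold. Let L be income lost through illness, which may or may not be deducted from R.

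- If S = 0, then S / R = 0 and S / (R − L) = 0 for any L smaller than R. With no spending the indicator is negative however much income is lost.
- If S > 0 and resources are measured by current income, S / (R − L) is larger than S / R. Lost income then raises the ratio, but the result mixes spending with loss.
- Impoverishment depends on its definition. If it subtracts only health spending from household resources, L does not enter as a loss due to illness. If it counts lost income, L enters, but only where it carries the household across the poverty line.
- Work days missed without loss of income change neither indicator under any of these definitions.

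**Step 3: typical cases.**

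| Person with an NCD | Catastrophic expenditure | Impoverishment | Productivity loss |
| --- | --- | --- | --- |
| Insured, no spending, misses work, income unchanged | No | Not from this loss | Yes |
| Insured, no spending, loses income | No | Only if lost income counts and the poverty line is crossed | Yes |
| Spends and loses income | Possible, driven by both | Possible | Yes |
| Spends heavily, no work lost | Possible | Possible | No |

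The mismatch runs both ways. The first two rows can be missed, and the last can be counted although no work was lost.

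**Step 4: whether another analysis fills the gap.** The descriptive statistics cover economic losses but test no association. The mixed models and analyses of variance take indirect cost as an outcome, but the predictor named is distance. The later ANOVA compares mean spending by revenue source. No section names days lost or income lost as an outcome to be tested against NCD status.

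**The case against.** The strongest reply has three parts.

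First, the sentence can be parsed differently. It lists two outcomes joined by and/or, and the closing clause on indicators may belong to financial hardship alone. Productivity loss would then simply lack a named metric, and choosing one could be left to a statistical analysis plan that is not at hand. The parsing is possible, but it does not rescue the text: the regression is still said to assess productivity loss, and the protocol still gives it no outcome for doing so. The wording needs correcting on either reading.

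Second, a reader might infer that lost days and lost income contribute nothing to the two indicators and that this part of the burden is missed entirely. The documents do not support that. Impoverishment is undefined and could count lost income, and an income-based denominator would let lost income raise the catastrophic-expenditure ratio. The defensible statement is partial and indirect capture of income, and none of work days as such.

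Third, a reader might infer that indirect cost goes unanalysed. That is also too strong. The first objective asks for quantification, and the descriptive analysis addresses it. Economic losses are described for people with hypertension and/or diabetes, and indirect costs are modelled against distance.

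It is also tempting to add that the exposure pools people in care with undiagnosed people found at screening, and to put a number on the resulting dilution. The documents give no share of people with an NCD who are out of care. They also do not say which survey feeds this regression, and NCD patients interviewed at facilities are in care by design. No dilution figure can be supported, and NCD status as a whole is a legitimate population contrast.

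**Conclusion.** The point holds in a limited form. As stated, the regression cannot properly test whether hypertension and/or diabetes is associated with the productivity burden that Research Question 1 describes. The only indicators named are one that does not measure missed work and one that, depending on an unstated definition, captures lost income at most in part. The gap is confined to the tested association with NCD status and does not extend to the descriptive quantification of indirect cost.

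No numerical size can be given. The conclusion rests on reading catastrophic health expenditure as a spending measure, as its name says, and on the protocol's own separation of direct-cost hardship from lost work and income. It does not depend on thresholds or definitions, which may properly wait for the analysis plan. It should be corrected because the protocol itself names the indicators and, as worded, offers them for an outcome they do not fit.

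**What to change.** In Analytical Methods, split the sentence in two. Keep catastrophic health expenditure and impoverishment as the indicators of financial hardship. Then add a separate regression with NCD status as the exposure, and with work days lost and income lost through illness, by the patient and by a caregiver, as the outcomes. The form of the model, the recall period and the definitions of the two hardship indicators can be left to the analysis plan.

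The cost is a reworded sentence and one extra model. Productivity-loss data are already planned in the household survey. The questionnaire is not among the documents at hand, so check that it records days and income separately, covers caregivers, and asks the same items in the exit survey.

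As an optional secondary analysis, NCD status could be split into no NCD, NCD not in care and NCD in care, in line with the distinction that Analytical Methods already draws for its logistic regressions. The main correction does not depend on it.

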- Other means of support from the social network, such as accompaniment to the health facility, or offering transport to the health facility

- Social health protection, or other forms of social protection (CHF, NHIF, TASAF, etc.)

Egocentric social network analysis will then be used to analyse and visualise the network of actors and individuals that support people living with NCDs, and to characterise and quantify the function of a patient’s support network. Similar in concept to the more typical sociocentric social network analysis, egocentric social network analysis instead will analyse the composition and function of a network of actors in relation to a single entity; in this case, an individual with hypertension and/or diabetes). The main units of the egocentric social network analysis will be the composition of the patient’s support network (type of relationship, propinquity, age, gender, etc.), and the type of social support that is being received and provided (cash, personal care, clothing, etc.). The questionnaire instrument relevant to the proposed study has been included in this IRB submission package.

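### The ANOVA of spending by revenue source names no household effect, lists in-kind support without a valuation rule, and does not measure relative importance

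*Protocol*

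**What the plan says.** Protocol, Analytical Methods, plans the following: "An analysis of variance (ANOVA) of mean spending by revenue source will then be used to determine the relative importance of financial contributions". The sentence continues "from various household revenue streams to covering the costs of NCD care, such as" and gives five examples: earnings from work, sale of personal property, money from the social network, non-cash help from the social network, and social protection schemes. The fourth is worded "Other means of support from the social network, such as accompaniment to the health facility, or offering transport to the health facility".

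The text does not say which form of ANOVA is meant, and it names no household, village or facility term for this comparison. It gives no rule for putting a money value on the fourth item. Earlier in the same section, hypotheses on geographic and economic accessibility "will be explored using linear mixed models and analyses of variance", but that sentence does not cover the revenue-source comparison. The section ends with an egocentric network analysis that will record the type of support received, in cash and in kind.

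**The concern.** Three features of the planned analysis do not fit its purpose.

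- **Structure.** The levels being compared are streams of the same household. Amounts from one household are likely to be correlated: negatively if one source replaces another, positively if a large bill draws on several. A between-groups ANOVA ignores this.
- **Content.** One listed level is help in kind. It has no place in a comparison of mean spending unless a money value is assigned.
- **Target.** The aim is the relative importance of the sources. An F-test asks whether mean amounts are equal. It gives no measure of importance, and a few very large bills can dominate the means.

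At stake is the part of objective 1 that describes how people cope with the cost burden. The ranking of sources, and any claim that they differ, could reflect the method more than the households.

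**Working it through.** The Protocol gives no sample size, effect or SD for this ANOVA, so there is no planned figure to reproduce. The calculations below only show how much the missing household term could matter.

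**Inputs**

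- Significance level 0.05. It is stated for household expenditure ("power of 0.80, significance level of 0.05") and borrowed here.
- Households: "we will seek a total sample size of 390 households per district", so 2 × 390 = 780.
- Prevalence: "hypertension prevalence of 19.9% (95% CI: 17.1-22.9) for rural Tanzania". Illustrative n = 780 × 0.199 ≈ 155 households. Table 1 prints a total of 790, which would give 157 and changes nothing. Diabetes and the exit survey are left out, so n is only a convenient size.
- Number of sources k = 4 (without the in-kind item) or 5 (as listed).
- Within-household correlation ρ between source amounts: not given. Assumed range −0.2 to +0.5.

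**Step 1: algebra.** With equal variances σ² and common correlation ρ, the difference between two source means has variance 2σ²(1 − ρ)/n. A between-groups ANOVA assumes 2σ²/n. The ratio true/assumed is 1 − ρ:

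- ρ = −0.2: 1.2, so the true SE is √1.2 ≈ 1.10 times the assumed SE.
- ρ = +0.5: 0.5, so the true SE is √0.5 ≈ 0.71 times the assumed SE.

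The SE of one source mean, SD/√n from that source's own data, does not contain ρ.

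**Step 2: simulated type I error.** Equal true means, normal data, n = 155, 4,000 runs per setting (simulation SE about √(0.05 × 0.95/4000) ≈ 0.003):

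| ρ | Between-groups, k = 4 | Between-groups, k = 5 |
|---|---|---|
| −0.2 | 0.085 | 0.090 |
| −0.1 | 0.075 | 0.066 |
| 0 | 0.053 | 0.055 |
| +0.1 | 0.034 | 0.032 |
| +0.3 | 0.010 | 0.008 |
| +0.5 | 0.001 | 0.0005 |

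With household as a block, the rate is 0.044 to 0.057 at every ρ and both k.

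Step 1 agrees with this. For k = 5 the 5% critical value of F on 4 and 5 × 154 = 770 degrees of freedom is 2.38. At ρ = −0.2 the test in effect uses 2.38/1.2 = 1.98, which is exceeded about 9% of the time.

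**Step 3: data closer to spending.** Log-normal household totals were split among 4 sources by Dirichlet shares, with equal true means, n = 155 and 3,000 runs per setting:

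| Setting | Between-groups rejection |
|---|---|
| Mostly one source per household, moderate skew | 9.9% |
| Mostly one source per household, strong skew | 4.2% |
| Somewhat more mixing of sources, strong skew | 2.4% |
| All sources used together, moderate skew | 0.0% |

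With household as a block, the rate is 3.7% to 5.2%. All distributional settings are assumptions.

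**Step 4: the in-kind level.** Money from the social network is a separate item in the list, so the fourth item is non-cash. Entered as zero, it ranks last by definition. Entered at a money value, its rank depends on a rule that the Protocol does not state.

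**Step 5: means against importance.** In a constructed example, nine households in ten pay a cost c from earnings, and one pays 20c by selling property. Mean spending is 0.9c from earnings and 2c from sales, so sales rank first. Yet 90% of households use earnings, and the average household share is 90% against 10%. The ANOVA sees only the means.

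**The case against.** The strongest reply is that a reader might infer more than the text says. It is tempting to conclude that the Protocol specifies a one-way ANOVA, treats the amounts as independent, and will therefore report wrong p-values and error bars. The document does not support that. It says only ANOVA, which includes the repeated-measures form. Whether household enters as a block or random effect may be set out in a statistical analysis plan that is not shown. Near ρ = 0 the error rate is close to nominal, and within-household correlation leaves the SEs of single source means unchanged. The in-kind item is a problem of measurement and does not by itself invalidate any p-value.

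Nor is this the only analysis of coping strategies: descriptive statistics and the network analysis serve the same aim, and the latter already covers non-cash support. The questionnaire is not shown either. It may record a value for offered transport, and the layout, zeros and skew of the amounts are conjecture.

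All of this stands, and it limits the point. It does not remove it. A repeated-measures reading repairs the structure only. The unvalued in-kind level and the mismatch between a test of equal means and the stated target are visible in the Protocol itself.

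**Conclusion.** The point holds in a limited form. The Protocol plans an ANOVA across a within-household factor without naming a household effect, includes in-kind support in a comparison of spending without a valuation rule, and uses a test of equal means where relative importance is wanted.

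If the ANOVA were run between groups, rejection at a nominal 5% could lie anywhere from about 10% to about 0%. The direction depends on a correlation that is not known in advance, so a reader could not correct for it. That range rests on assumed n, correlations and distributions. The in-kind and target problems need no such assumptions. The analysis is secondary and no sample size depends on it, so the point is worth correcting but does not threaten the study.

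**What to change.** Replace the ANOVA with two summaries for each cash source: the proportion of households using it, and its share of the household's NCD cost. Give 95% intervals that account for clustering by village (household survey) and facility (exit survey), for example from a bootstrap that resamples villages and facilities. If a model is wanted, state that household enters as an effect, in a repeated-measures or mixed model.

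Report in-kind support separately, as yes/no or a count, for example alongside the planned network analysis. Otherwise, state the rule by which it is valued.

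The cost is a change of wording and a small amount of analysis work, provided the questionnaire records amounts by source. That should be confirmed, since the instrument is not shown.
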